|                                                                                     |                                                                                     |                                                                                     |                                                                                      |                                                                                       |

[figure not shown]

Acceptability survey – Study A. IRAS ID: 291254

Document version 1.0.0 – 06-10-2020

Study ID:

| As a result of your visit to the doctor today do you feel you are | Much better              | Better                   | Same or less             | Not applicable           |
|-------------------------------------------------------------------|--------------------------|--------------------------|--------------------------|--------------------------|
| able to cope with life?                                           |  |  |  |  |
| able to understand your illness?                                  |  |  |  |  |
| able to cope with your illness?                                   |  |  |  |  |
| able to keep yourself healthy?                                    |  |  |  |  |
|                                                                   | Much more         | More              | Same or less      | Not applicable    |
| confident about your health?                                      |  |  |  |  |
| able to help yourself?                                            |  |  |  |  |

**Further comments:**

|  |
|--|
|  |
|  |
|  |
|  |
|  |
|  |

**Thank you for taking the time to complete this survey.** The research team really appreciates your involvement in this study. If you have any questions, please ask the researcher.

[figure not shown]

B to P survey – Study A. IRAS ID: 291254

Document version 1.0.0 – 13-01-2021

Study ID:

Title of Project:

## HbA1c Target Achievement in diabetes study (ATTAINS study) – Barriers to Participation

IRAS ID: 291254

(Form to be on headed paper)

Name of Researcher: [name]

Chief Investigator: [name]

We have been asking people to take part in diabetes research. People often have many good reasons to decline taking part. We would like to ask you a few questions to see what we could do in the future to help more people take part in research.

To what extent do you agree or disagree with these statements about taking part in research:

| 1) My work commitments stopped me from taking part in research.                                       |                                                                                              |                                                                                                |                                                                                                  |                                                                                                            |
|-------------------------------------------------------------------------------------------------------|----------------------------------------------------------------------------------------------|------------------------------------------------------------------------------------------------|--------------------------------------------------------------------------------------------------|------------------------------------------------------------------------------------------------------------|
| Strongly Agree
[figure not shown] | Agree
[figure not shown] | Neutral
[figure not shown] | Disagree
[figure not shown] | Strongly Disagree
[figure not shown] |
| Comments:                                                                                             |                                                                                              |                                                                                                |                                                                                                  |                                                                                                            |

| 2) I am a person with a disability, which makes it difficult to take part in research.                |                                                                                              |                                                                                                |                                                                                                  |                                                                                                            |
|-------------------------------------------------------------------------------------------------------|----------------------------------------------------------------------------------------------|------------------------------------------------------------------------------------------------|--------------------------------------------------------------------------------------------------|------------------------------------------------------------------------------------------------------------|
| Strongly Agree
[figure not shown] | Agree
[figure not shown] | Neutral
[figure not shown] | Disagree
[figure not shown] | Strongly Disagree
[figure not shown] |
| Comments:                                                                                             |                                                                                              |                                                                                                |                                                                                                  |                                                                                                            |

[figure not shown]

B to P survey – Study A. IRAS ID: 291254

Document version 1.0.0 – 13-01-2021

Study ID:

| 3) I did not understand what the research is about.                               |                                                                                   |                                                                                   |                                                                                    |                                                                                     |
|-----------------------------------------------------------------------------------|-----------------------------------------------------------------------------------|-----------------------------------------------------------------------------------|------------------------------------------------------------------------------------|-------------------------------------------------------------------------------------|
| Strongly Agree                                                                    | Agree                                                                             | Neutral                                                                           | Disagree                                                                           | Strongly Disagree                                                                   |
| [figure not shown] | [figure not shown] | [figure not shown] | [figure not shown] | [figure not shown] |
| Comments:                                                                         |                                                                                   |                                                                                   |                                                                                    |                                                                                     |

|                                                                                                                                                                                                                                                                                                                                                                                          |                                                                                     |                                                                                     |                                                                                      |                                                                                       |
|------------------------------------------------------------------------------------------------------------------------------------------------------------------------------------------------------------------------------------------------------------------------------------------------------------------------------------------------------------------------------------------|-------------------------------------------------------------------------------------|-------------------------------------------------------------------------------------|--------------------------------------------------------------------------------------|---------------------------------------------------------------------------------------|
| 
4) - A language barrier prevented me from taking part in the research.
 
- Bariera językowa uniemożliwiła mi udział w badaniach.
 
- Zúčastniť sa na výskume mi bránila jazyková bariéra.
 
- 语言障碍使我无法参与研究
 
- Isang hadlang sa wika ang pumigil sa akin na makilahok sa pagsasaliksik.
 
- ஒரு மொழித் தடை என்னை ஆராய்ச்சியில் பங்கேற்கவிடாமல் தடுத்தது.
 |                                                                                     |                                                                                     |                                                                                      |                                                                                       |
| Strongly Agree                                                                                                                                                                                                                                                                                                                                                                           | Agree                                                                               | Neutral                                                                             | Disagree                                                                             | Strongly Disagree                                                                     |
| [figure not shown]                                                                                                                                                                                                                                                                                                      | [figure not shown] | [figure not shown] | [figure not shown] | [figure not shown] |
| Comments:                                                                                                                                                                                                                                                                                                                                                                                |                                                                                     |                                                                                     |                                                                                      |                                                                                       |

| 5) I do not have enough time to take part in this research.                         |                                                                                     |                                                                                     |                                                                                      |                                                                                       |
|-------------------------------------------------------------------------------------|-------------------------------------------------------------------------------------|-------------------------------------------------------------------------------------|--------------------------------------------------------------------------------------|---------------------------------------------------------------------------------------|
| Strongly Agree                                                                      | Agree                                                                               | Neutral                                                                             | Disagree                                                                             | Strongly Disagree                                                                     |
| [figure not shown] | [figure not shown] | [figure not shown] | [figure not shown] | [figure not shown] |
| Comments:                                                                           |                                                                                     |                                                                                     |                                                                                      |                                                                                       |

[figure not shown]

B to P survey – Study A. IRAS ID: 291254

Document version 1.0.0 – 13-01-2021

Study ID:

| 6) I am a person with other physical or mental health problems that prevent me from taking part in research. |                                                                                   |                                                                                   |                                                                                    |                                                                                     |
|--------------------------------------------------------------------------------------------------------------|-----------------------------------------------------------------------------------|-----------------------------------------------------------------------------------|------------------------------------------------------------------------------------|-------------------------------------------------------------------------------------|
| Strongly Agree                                                                                               | Agree                                                                             | Neutral                                                                           | Disagree                                                                           | Strongly Disagree                                                                   |
| [figure not shown]                            | [figure not shown] | [figure not shown] | [figure not shown] | [figure not shown] |
| Comments:                                                                                                    |                                                                                   |                                                                                   |                                                                                    |                                                                                     |

| Further comments: |
|-------------------|
|                   |
|                   |
|                   |
|                   |
|                   |
|                   |

**Thank you for taking the time to complete this survey.** The research team really appreciates your feedback. If you have any questions, please ask the researcher.

Patient interview topic guide and protocol (Study B)

**Venue:** Via telephone

**Please ensure a quiet and distraction-free environment for the interview. Study B interview dates and times should be arranged during patient visits to the diabetes centre during Study A final visit. Interviews should be carried after participants have completed study A.**

**Proposed duration:** 15 – 30 minutes.

**Structure:** Call participant and inform them that the call is recorded for research purposes and that their data will remain confidential. Briefly summarise the purpose of the study. Ensure participant has read and understood Study B participant information sheet. Answer any questions they may have. Consent already obtained during Study A.

**The interview will begin, (start audio recording):**

([Topics](#) in blue, underlined. Themes identified in **bold**. Probing questions indented)

Greet participant, introductions.

"Please tell me, how long have you had diabetes?" (*easy question/ice-breaker*)  
"How were you diagnosed/what happened?"

Perceptions on the use of 'A1c' targets

**"What do you know about the goals/targets for your 'A1c'?"**

"What do these mean personally for you?"

"Why do you think 'A1c' is important?"

**"How did you feel about being given an 'A1c' target in the study?"**

"Did it make you feel driven to do better?"

"Did it make you disheartened and demotivated?"

"If you were doing well, did it make you relax your efforts towards your diabetes?"

"Did it make you feel elated?"

"If you weren't doing well, did it make you more motivated or less motivated?"

**"Had you been given an 'A1c' target before the study?"**

"How did it make you feel?"

"Why did it make you feel like this?"

**"What is your opinion on using 'A1c' targets in people with diabetes?"**

Individualisation of 'A1c' targets

"There is a lot of research that tells us that **people with diabetes should be given individualised goals for 'A1c'**. What are your views about this?"

"Can you tell me more about that?"

"In your opinion, what are the positive things about having an 'A1c' target?"

"In your opinion, what are the negative things about having an 'A1c' target?"

**Transcribe the interview as soon as possible after completion.**

Document ref: ATTAINS Study – Study B – patient interview guide – v 1.0.0 – 12-10-2020

[figure not shown]

Healthcare professionals interview topic guide and protocol  
(Study C)

**Venue:** Via telephone/video call

**Ensure a distraction-free environment is located for telephone/video calls. Ensure the interview has appropriate access to telephone/video call facilities within the trust. Study C interview dates and times should be arranged via email with the healthcare professional.**

**Proposed duration:** 15 – 30 minutes.

**Structure:** Call participant and inform them that the call is recorded for research purposes and that their data will remain confidential. Briefly summarise the purpose of the study. Ensure participant has read and understood Study C participant information sheet. Answer any questions they may have. Ensure consent form has been completed.

**The interview will begin, (start audio recording):**

([Topics](#) in blue, underlined. Themes identified in **bold**. Probing questions indented.)

Greet participant, introductions.

“Can you tell me a little bit about your professional background as a diabetes healthcare professional?” (easy question/ice-breaker)

#### Perceptions on the use of HbA1c targets

“HbA1c targets are universally used to aid management decisions in people with diabetes. We know it is beneficial to help patients achieve these targets. **What do you think patients’ understanding of HbA1c is?”**

“**What sort of discussions would you normally have with a patient on the topic of HbA1c?”**

“**What do you think patients’ views on HbA1c targets are?”**

“What do you think could be done to help improve patient perceptions of HbA1c?”

“**What are your views on the use of HbA1c targets in people with diabetes?”**

“**What are the main advantages and disadvantages to using HbA1c targets in the management of people with diabetes?”**

“**If you knew that HbA1c targets had an impact on the mental health of people with diabetes, in what way would it change your discussions with patients?”**

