#### **4.1 Objectives**

Using a mixed-methods approach, these related studies aim to explore:

1. the feasibility of evaluating the use of explicit glycaemic targets in people with diabetes.
2. the preliminary impact of setting explicit glycaemic targets on psychometric and glycaemic outcomes in people with diabetes.
3. the experiences, views and opinions of people with diabetes on the acceptability of study processes and glycaemic target-setting in the context of their diabetes care.
4. the experiences, views and opinions of diabetes healthcare professionals on the use of glycaemic target-setting and the individualisation of glycaemic targets in people with diabetes.
5. the experience, views and opinions of people declining entry into study A on barriers to participation in diabetes research.

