#### Individualisation of HbA1c targets

A lot of research has suggested that HbA1c targets should be individualised to the patient.

“**How has this informed your practice?”**

“**What approach do you take to individualising HbA1c targets?”**

“Have you found that this is beneficial?”

“If so, in what way?”

“If not, why not?”

“**In what way would you say HbA1c target-setting in people with diabetes could be improved?”**

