**“Do you think setting HbA1c targets in people with diabetes has an impact upon their mental health?”**

**“How can healthcare professionals be supported to deliver better care for people with diabetes?”**

**Probing:**

Active listening to guide further questioning

Appropriate use of silence

Politely interrupt and re-focus the interview if going off-topic

Clarify/elaborate/expand

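### All three interview guides cite research favouring individualised HbA1c targets before asking about them, and the Study C guide raises a mental-health effect of targets before asking whether one exists

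*Protocol*

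**What the plan says.** Research question 4 (Protocol, Section 4) assigns to Study C the views of healthcare professionals on target-setting and on individualised treatment targets. Objective 4 (Section 4.1) likewise covers "the experiences, views and opinions of diabetes healthcare professionals on the use of glycaemic target-setting" together with individualisation. Section 4.2 lists the personalisation of targets among the topics on which the interviews will capture patient and professional perspectives. The Background (Section 1) describes the psychological impact of HbA1c goal-setting as unknown.

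The Study C guide opens its block on perceptions of targets with a premise that includes "We know it is beneficial to help patients achieve these targets". Later in that block it asks "What are your views on the use of HbA1c targets in people with diabetes" and "What are the main advantages and disadvantages to using HbA1c targets in the management of people with diabetes". The block ends with a hypothetical that begins "If you knew that HbA1c targets had an impact on the mental health of people with diabetes" and asks how this would change discussions with patients. The next block opens with "A lot of research has suggested that HbA1c targets should be individualised to the patient". The last block, on diabetes and mental health, asks "Do you think setting HbA1c targets in people with diabetes has an impact upon their mental health".

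The Study B and Study D guides introduce individualisation with the same preface, which begins "There is a lot of research that tells us that" and goes on to say that people with diabetes should have individualised A1c goals. Both then ask for the interviewee's views on that statement.

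**The concern.** An interviewee who has just heard that research supports a position is more likely to agree with it, or to answer within its terms. The same applies to someone asked to imagine an effect before being asked whether it exists.

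Two stated objects of the qualitative work are exposed: views on individualisation, and, in Study C, belief in a mental-health effect of targets. Section 3 of the Protocol plans to triangulate the interview findings with Study A to help judge whether a larger study is justified. Triangulation is worth less if one source was steered towards the expected answer.

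The setting may add to the pull. Study C recruits within the Trust that sponsors the work, and the researcher is a doctor in the same diabetes centre (Sections 5.3 and 7.3.1).

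**Working it through.** No formula applies. The check is to read each guide in order and ask, for each topic, what the interviewee has been told before the first question on it.

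**Individualisation**

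- Study B: the research endorsement comes first, then a request for views on it, then probes on positive and negative aspects of having a target. An open question on targets in general comes earlier, but it does not mention individualisation.
- Study C: the endorsement comes first. The questions that follow ask how it has informed practice, what approach the respondent takes, whether this has proved beneficial (with follow-ups for yes and no), and how target-setting could be improved. None asks neutrally whether the respondent agrees with individualising.
- Study D: the same preface and sequence as Study B, after an open question on targets in general.

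Tally: the endorsement comes first in 3 of 3 guides.

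**Effect of targets on mental health or well-being**

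- Study B: the lead question openly asks how the interviewee felt about being given a target. The closed probes come after it and run both ways (motivated, disheartened, relaxed, elated). No answer is supplied first.
- Study C: the order is the premise on benefit, questions on patients' understanding and views, the open question on the respondent's own views, the question on advantages and disadvantages, the hypothetical, the individualisation block, and finally the direct question on whether an effect exists.
- Study D: no question asks about the psychological effect of targets. Its mental-health questions concern diabetes itself.

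Tally: an effect is suggested before the direct question in 1 of 3 guides (Study C).

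**Reach**

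Planned samples are 15 each for Studies B, C and D (Section 7.2.1).

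- Endorsement preface: 15 + 15 + 15 = 45 planned interviews.
- Order problem: 15 planned interviews.

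These are counts of interviews exposed, not estimates of bias, and Section 7.2.1 allows all three samples to be adjusted.

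**The case against.** A reader might infer that Studies B, C and D cannot yield any unprompted view on the effect or the individualisation of targets. The documents do not support that, for several reasons.

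- Study B asks about the effect openly and with two-sided probes. Study D does not ask about it, and its research question is barriers to participation. The questions on barriers come before those on targets.
- The Study C hypothetical is a conditional about practice and does not assert that an effect exists. It follows an open question and a balanced one, so a respondent can raise a psychological effect unprompted.
- The statement that achieving targets is beneficial says nothing about mental health, and a request for disadvantages follows it.
- Study C respondents are diabetes professionals. The Protocol describes individualised targets as common in secondary care (Abstract), so the endorsement tells them little that is new. The Study C guide also has a follow-up for those who have not found individualisation beneficial.
- Interviews are recorded and transcribed verbatim, so the position of each remark relative to a prompt is kept and can be coded. It would be wrong to say that no analysis could separate prompted from spontaneous views.
- The interviews are semi-structured, so the interviewer may depart from the written order. None of the green progression criteria in Section 8.9 rests on these answers.

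All of this narrows the point. It does not remove it. Coding by position helps only where an unprompted opening exists. For individualisation none of the three guides contains one, beyond what an interviewee happens to volunteer. The chance to disagree in Study C comes after the endorsement and concerns benefit found in practice, not agreement in principle. Flexibility in the interview is a weak safeguard when the premise is written into the guide.

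**Conclusion.** The point holds in a limited form. All three guides endorse individualisation before asking about it. This matters most in Study C, where views on individualised targets are part of the research question and agreement is never neutrally sought. It matters less in Study B, and in Study D it is only a matter of consistency.

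Separately, Study C answers to the direct question on a mental-health effect may be primed by the earlier hypothetical, although spontaneous mentions in the earlier open questions remain usable. Study B's evidence on how the target felt is not affected by this ordering.

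The size of any bias cannot be derived from the Protocol. The conclusion assumes that interviewers broadly follow the written order. It also assumes that the Study B guide is complete as seen: the available text shows no probing or closing section for it, unlike those for C and D, so later Study B questions cannot be judged.

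**What to change.** Make these changes before interviewing starts, because an answer given after a prompt cannot be collected again unprompted.

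1. Study C guide: ask the direct question on whether targets affect mental health before the hypothetical, and keep the hypothetical as a follow-up.
2. Study C guide: drop the statement that achieving targets is known to be beneficial, or move it after the questions on views, advantages and disadvantages.
3. All three guides: open the individualisation topic with a neutral question, for example: What are your views on setting different HbA1c targets for different people? Keep the sentence about research only as a later probe.

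The cost is a wording and order revision of three guides, with the sponsor deciding how the amendment is classified (Section 8.2.2). It needs no extra participants, visits or staff. The neutral opening question adds little or no interview time.
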